### Outcomes

The primary outcome will be the number of smokers who referred by secondary school students to YQL at T4 (at the end of the 6-month competition). Secondary outcomes include the reach, adoption, implementation, maintenance, and other effectiveness measurements.

### Measurements

Demographic data including age, sex, household size, household income, living district, and smoking status of the secondary school students and participating nursing students will be collected at T1.The Reach Effectiveness Adoption Implementation Maintenance (RE-AIM) framework will be adopted [25].Reach will be recorded as: 1) the number and proportion of secondary schools, 2) secondary school students, and 3) nursing students reached; 4) the number of workshops conducted; 5) the numbers of ASAs in the workshops and that passed the examinations (involving a written test and an oral demonstration; the oral examination will be assessed through role-play assessments); 6) the number of outreach sessions conducted; 7) the number of smokers reached in the outreach sessions; 8) the number of counseling sessions in which ASAs were involved; and 9) the number of smokers that the ASAs involved in counseling sessions. Measurements from 7) to 9) will be recorded in log sheets with the exact time and date by ASAs. Other numbers will all be recorded in log sheets with the exact time and date by the RA.Effectiveness will be recorded in terms of: 1) the number of smokers refer by secondary school students to YQL (primary effectiveness measure), 2) the level of secondary school students’ knowledge in smoking cessation and AWARD model (will be assessed by asking ASAs to respond “True/False/Don’t know” to 19 related statements at T1–T5), 3) practice (such as asking the secondary school students the number of times delivering the brief intervention and the number of smokers who receive their brief interventions) and attitudes toward smoking cessation and AWARD model (will be recorded by asking ASAs to respond to 31 related items at T1–T5), 4) self-efficacy in using AWARD model (will be assessed by asking ASAs to answer 3 items (scale 1–10) at T1–T5). The scales have all been used in various smoking cessation projects [7, 11, 13, 14].Adoption: the numbers and proportions of 1) ASAs and 2) nursing students adopting the brief interventions with AWARD model to smokers. The number of ASAs who join the smoker referral competition will be recorded by the RA in log sheets with the exact time and date. The intention of ASAs and nursing students to conduct the brief interventions with AWARD model in the future at T2-T5 will also be assessed.Implementation: 1) facilitating factors, 2) barriers, and 3) feasibility for implementing the project. These factors will be explored using semi-structured interviews with the responsible teachers in the participating secondary schools, ASAs, participating nursing students, and responsible staff in YQL at T2.Maintenance, or the effectiveness of the project in long term will be measured at T5: 1) the number of smokers referred to YQL by secondary school students, 2) the level of secondary school students’ knowledge in smoking cessation and the AWARD model, 3) practice and attitude towards smoking cessation and AWARD model, and 4) self-efficacy in using AWARD model. At the setting level, the components that were maintained in the project at T5 will be assessed using semi-structured interviews with ASAs and participating nursing students.

### Data analysis

Quantitative data will be analyzed using SPSS. Descriptive statistics will be reported (objectives 5 and 6). The characteristics of ASAs and nursing students who intend to use the AWARD model in the future will be compared with those who do not (adoption) using independent sample t-tests and chi-square tests (objective 6). Mixed between-within-subjects analysis of variance and odds ratios with logistic regression will be used to examine the differences in outcomes between the ASAs and the control group (objectives 1–4) at each follow-up. Intention-to-treat analyses and multiple imputation will also be used.

QSR NVivo will be used to organize the qualitative data from the interviews (objective 7) and reflective journals. ASA’s reflective journals will be particularly analyzed for the effects of our program in helping ASAs to refer smokers to YQL, ASAs’ level of knowledge, practice and attitude in smoking cessation and the AWARD model, and self-efficacy in using the AWARD model (objective 1–4). Content analysis [26] will be performed by two authors ([name] and [name]) separately by applying bracketing. Descriptions will be returned to participants for checking and feedback. Any discrepancies will be discussed and resolved in regular meetings among team members.

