### Clusters and randomization

14 clusters (14 schools) will be randomized to the intervention or control group using a 1:1 ratio by a research assistant (RA) who is not from our team using an independent computerized randomization sequence process that can only be accessed by that RA to ensure allocation concealment. This RA will login to an online platform to perform randomization. Randomization sequences will be generated by the computer in randomly permuted blocks sizes of 2, 4, and 6. The RA responsible for recruitment will record the exact date and time of recruitment. Computerized time stamps and electronic logs of sent allocation will be used to ensure allocation concealment. The RA undertaking recruitment will be responsible for data collection and be blinded to the group assignment.

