### Sample size calculation

G*Power [22] was used based on a small-to-medium effect size on the primary outcome, i.e. number of smoker referred by secondary school students at the 6-month follow-up (d = 0.35), based on our team’s experience in smoking cessation projects [11–13]. Hence, to detect a significant difference in the number of smoker referred between the two groups with a significance level of 5% and power of 80%, a total of 260 secondary school students would be needed. Based on a conservative estimation, around 360 eligible secondary school students can be approached in each school. The response rate for previous workshops of a similar duration was around 8% conservatively [11, 23]. Hence, we expect to recruit 28 (360 × 0.08) students in each school. For cluster RCT, it is estimated that the intracluster correlation coefficients = 0.01, and the design factor = (1+(28–1)*0.01) = 1.27, then the sample size needed will be 331 (260*1.27). With an estimated 10% attrition rate at 12 months, the total sample size needed will be 368 students (331/0.9) with 184 students in each group. Thus, a total of 14 schools with 7 schools (184/28) in each group are needed.

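### Schools are randomised and the sample size allows for clustering, but the methods named for the between-arm comparisons do not, in standard form, account for school

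*Protocol article*

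**What the plan says.** Under Clusters and randomization, the unit of allocation is the school: "14 clusters (14 schools) will be randomized to the intervention or control group using a 1:1 ratio".

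The Sample size calculation section accepts that students in one school are correlated. It says "it is estimated that the intracluster correlation coefficients = 0.01", takes 28 students per school, and multiplies the unclustered total of 260 by 1.27 to reach 331. Allowing for 10% attrition at 12 months gives 368 students, 184 per arm.

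The Data analysis section then names the methods for comparing the two arms: "Mixed between-within-subjects analysis of variance and odds ratios with logistic regression will be used to examine the differences in outcomes between the ASAs". This covers objectives 1 to 4 at each follow-up. It adds intention-to-treat analysis and multiple imputation. The abstract names the same two methods. The article nowhere mentions a school effect, generalised estimating equations (GEE), cluster-robust standard errors or a school-level comparison.

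**The concern.** The design and the sample size treat the school as the unit that carries the random variation. The named analyses do not.

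A mixed between-within-subjects ANOVA is the split-plot design, with group as the between-subjects factor and time as the within-subjects factor. It allows for correlation among the five assessments of one student, not among students of one school. Logistic regression in its usual form assumes independent students.

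Inflating the sample size restores power that clustering would otherwise remove. It leaves the standard error of a student-level test too small. If the section is followed as written, the between-arm tests of referrals (the primary outcome), knowledge, practice and attitudes, and self-efficacy would reject too often under no effect, and their confidence intervals would be too narrow. The error favours a claim of effectiveness.

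**Working it through.** **Inputs from the Sample size calculation and Clusters and randomization sections:** d = 0.35, 5% significance, 80% power, 28 students per school, ICC 0.01, 10% attrition at 12 months, 7 schools per arm. Sidedness is not stated; two-sided is used because it reproduces the plan's figure.

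**1. The plan's own figures.**
- A two-sample t-test at two-sided 5%, d = 0.35 and 80% power needs 130 per arm, or 260 in total. One-sided would give 204.
- Design factor: 1 + (28 − 1) × 0.01 = 1.27.
- 260 × 1.27 = 330.2, rounded up to 331.
- 331 / 0.9 = 367.8, rounded up to 368.

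All three totals reproduce.

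**2. Analysed students per school.** 368 / 14 = 26.3 if all are followed, and 331 / 14 = 23.6 (about 24) after 10% attrition. The plan's nominal figure is 28.

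**3. True type I error of a student-level test.** With design effect DE = 1 + (m − 1) × ICC, a test that ignores school has a true two-sided error of about 2 × [1 − Φ(1.96 / √DE)]. The ratio of its interval width to the width allowing for clustering is 1 / √DE.

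| Analysed per school | ICC | DE | True type I error | Width ratio |
|---|---|---|---|---|
| 23.6 | 0.01 (protocol) | 1.226 | 7.7% | 0.90 |
| 23.6 | 0.03 (assumed) | 1.679 | 13.0% | 0.77 |
| 23.6 | 0.05 (assumed) | 2.132 | 18.0% | 0.68 |
| 28 | 0.01 (protocol) | 1.27 | 8.2% | 0.89 |

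First row: √1.226 = 1.107; 1.96 / 1.107 = 1.770; 2 × [1 − Φ(1.770)] = 0.077.

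**4. Check by simulation** (20,000 trials, 7 v 7 schools, normal data, no effect). With 24 per school, the student-level t-test rejected in 7.7% of trials at ICC 0.01 and 17.7% at 0.05. A t-test on the 14 school means (12 df) rejected in 5.1% and 4.9%. With 28 per school at ICC 0.01, the figures were 8.5% and 5.1%.

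**5. Interval width after the change.** Moving from the student-level test to a 12-df school-level analysis, at 23.6 per school and ICC 0.01, multiplies the width by √1.226 × 2.179 / 1.967 = 1.107 × 1.108 = 1.23. About half of the widening comes from the design effect and half from the t reference on 12 df.

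**6. Power of a 12-df school-level test, d = 0.35, ICC 0.01.** The noncentrality is 0.35 / √(2 × DE / n), where n is the number analysed per arm.
- 23.6 per school: n = 165.5, SE = √(2 × 1.226 / 165.5) = 0.122, noncentrality 2.88, power about 75%. The normal approximation gives 82%.
- 26.3 per school: n = 184, DE = 1.253, power about 79%.
- 28 per school: n = 196, DE = 1.27, power about 81%.

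**The case against.** The article does not say that students will be treated as independent. It names two families of method in one sentence, with no covariates, random terms or variance estimator. SPSS can fit clustered versions, and the sample size section shows that the authors know about clustering. A fuller analysis plan may contain a school term. A reader might infer that the authors chose to ignore clustering, but the text does not support that. What can be said is that the methods as named, in standard form, do not account for school. This still stands as more than missing detail: specific methods are attached to the primary objective, and they do not fit the unit of randomisation.

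Three wider readings fail.
- A reader might extend the fault to the t-tests and chi-square tests in the same section. Those compare participants who intend to use the AWARD model with those who do not (objective 6), including nursing students. They do not compare the randomised arms.
- A reader might conclude that every secondary outcome is affected. Reach is recorded as counts and proportions, and implementation is explored in interviews. Neither has a between-arm test.
- A reader might quote 13% or 18% as the trial's error rate. Those figures need ICCs that the documents do not give. The only documented value is 0.01.

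The percentages also come from a Gaussian comparison at one time point. The primary outcome is a count, possibly with many zeros: the Introduction reports that 1% of participants in an earlier programme had referred smokers. The figures show direction and rough size, not the exact error rate of the planned model.

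**Conclusion.** The point holds for the between-arm comparisons under objectives 1 to 4: referrals, knowledge, practice and attitudes, and self-efficacy, including their 12-month versions. Followed as written, in standard form, a nominal 5% test would have a true level of about 7.7% to 8.2% at the protocol's own ICC. Its nominal 95% interval would be about 10% to 11% too narrow. The excess is moderate at ICC 0.01 and grows quickly if the true ICC is higher.

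The conclusion assumes that no school term is supplied in a document not shown, that schools are of equal size, and that the Gaussian approximation is fair for the outcome. It needs correction before outcomes are analysed because it concerns the validity of the primary test.

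**What to change.** Amend the Data analysis section so that the between-arm analyses for objectives 1 to 4 account for school. Either of these would do:
- a mixed model with school as a random effect, or GEE with school as the cluster, with a small-sample correction because there are only 7 schools per arm, and in a form suited to a count for the primary outcome;
- a comparison of the 14 school-level means or rates.

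Include school in the imputation model. The objective 6 comparisons need no change on this account.

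The change needs no new data or visits, but it is not free. At ICC 0.01 the interval becomes about 23% wider than that of the student-level test. Power for d = 0.35 on 12 df is about 75% with 24 analysed per school, 79% with 26 and 81% with 28. The 10% attrition is projected to 12 months and the primary time point is 6 months, so the figure for the primary outcome may lie between the first two. The stated 80% should be restated accordingly.

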### Data collection

After randomization, responsible teachers in schools will first be briefed by our RA about the purpose and protocol of the project. The schools will then distribute our promotional leaflets, information sheet and consent forms to students or parents depending on schools’ preferences. Consent forms with students’/parents’ telephone numbers will be returned to teachers if students are interested in joining the project. Eligible students will be informed by our RA via telephone that their participation will be voluntary and confidentiality will be maintained. They will also be notified about the details and schedule of the program activities.

The RA will contact the students in the intervention and control group at the start of training program (T1), at the end of training program (T2), and at 3 (T3), 6 (T4), and 12 months (T5) after the end of the training program by telephone to complete a set of questionnaires.

At T2, each ASA will submit a 300-word reflective journal. Responsible teachers in participating secondary schools, participating nursing students, ASAs, and responsible YQL staff will be randomly invited to complete a one-to-one semi-structured interview focused on implementation. The interviews will be conducted by an RA at T2 until data saturation is reached.

At T5, ASAs and nursing students will be interviewed about maintenance. Another RA who is not involved in this project will be asked to generate random numbers using a computer for random selection of participants for the interviews. All interviews will last for around 15–30 minutes and be audio-recorded in a room in our university or online (e.g., via Zoom) depending on the preference of interviewees. Based on the interview guide developed by our team, they will be asked about their overall experience, facilitating factors, barriers, and feasibility of implementing brief interventions using the AWARD model to smokers at T2. At T5, they will be asked about the maintained effects and components of the project. It is estimated that around 40 and 20 interviewees will be needed to reach data saturation at T2 and T5, respectively. Each interviewee will receive HKD$200 as a travelling allowance.

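### For the secondary scores (objectives 2–4) the named mixed ANOVA carries no baseline covariate although T1 scores are collected, so it is less precise than a model that conditions on T1

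*Protocol article*

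**What the plan says.** The Data analysis section of the protocol article gives one sentence on group comparisons: "Mixed between-within-subjects analysis of variance and odds ratios with logistic regression will be used to examine the differences in outcomes". The rest of that sentence sets out which arms are compared, for which objectives and when: "between the ASAs and the control group (objectives 1–4) at each follow-up". No covariate is named, and the levels of the within-subject factor are not listed.

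Data collection sets five contacts, beginning "at the start of training program (T1), at the end of training program (T2"), then 3, 6 and 12 months after training ends. Measurements places the knowledge, practice/attitude and self-efficacy items at all five. For self-efficacy the wording is that it "will be assessed by asking ASAs to answer 3 items (scale 1–10) at T1–T5". Every student should therefore have a T1 value on each of these scores.

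The primary outcome is different. It is the number of smokers referred "to YQL at T4 (at the end of the 6-month competition"), and no T1 referral count is described.

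**The concern.** A mixed between-within ANOVA on a measure taken at T1–T5 would ordinarily treat T1 as one level of time. The baseline is then part of the response and is not conditioned on. If T1 is left out of the ANOVA, the baseline is not used at all. On either reading, information already collected is used less efficiently than it could be.

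What is at stake is the precision of the comparisons for objectives 2–4. The handling of T1 matters more here than in many trials. Only 14 schools are randomised, and Data collection has students invited after randomisation, once teachers have been briefed. Differences between arms at T1 are therefore plausible, whether by chance or by selection.

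**Working it through.** **Inputs from the protocol (Sample size calculation).** The effect size is for the "number of smoker referred by secondary school students at the 6-month follow-up (d = 0.35"), and "with a significance level of 5% and power of 80%, a total of 260 secondary school students would be needed". The design factor is 1.27 and attrition is 10%.

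**The plan's own figure.** A two-sample t-test with d = 0.35, two-sided 5% and 80% power needs 129.1, so 130 per arm and 260 in total. Then 260 × 1.27 = 330.2, rounded up to 331, and 331/0.9 = 367.8, rounded up to 368. The stated numbers reproduce. Working backwards, 368 × 0.9/1.27 ≈ 261, or about 130 effective students per arm.

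**Assumptions not in the documents.** Equal variance at all waves; equal between-wave correlation r, taken as 0.3, 0.5 or 0.7; a constant effect at T2–T5; d = 0.35 borrowed for the scores; the design factor unchanged by adjustment; no correction for having few clusters.

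**One follow-up visit.** Power comes from the noncentral t with noncentrality 0.35/√(2V/130), where V is the variance relative to a follow-up-only comparison. For V = 1 this is 2.82; for V = 0.75 it is 3.26. Each cell gives V, then power.

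| Analysis | V | r = 0.3 | r = 0.5 | r = 0.7 |
|---|---|---|---|---|
| T1 as covariate | 1 − r² | 0.91; 0.84 | 0.75; 0.90 | 0.51; 0.98 |
| Change from T1 | 2(1 − r) | 1.40; 0.66 | 1.00; 0.80 | 0.60; 0.95 |
| Follow-up only | 1 | 1.00; 0.80 | 1.00; 0.80 | 1.00; 0.80 |

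A normal approximation gives powers higher by less than 0.01. For any r between 0 and 1, 1 − r² is smaller than both alternatives. Change from T1 needs 2/(1 + r) = 1.54, 1.33 and 1.18 times the students of the covariate analysis. Follow-up only needs 1/(1 − r²) = 1.10, 1.33 and 1.96 times.

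**Sustained effect over T2–T5, with T1 as a wave.** The reference is the T2–T5 mean adjusted for T1, with variance (1 + 3r)/4 − r² = 0.385, 0.375 and 0.285.
- *Group main effect over five waves.* T1 carries no effect, so the contrast is 4/5 of the true one (0.35 becomes 0.28), with variance (1 + 4r)/5 = 0.44, 0.60 and 0.76. Relative efficiency is 0.64 × 0.385/0.44 = 56%, then 40% and 24%.
- *Group-by-time contrast (mean of T2–T5 minus T1).* There is no dilution. The variance is (1 + 3r)/4 + 1 − 2r = 0.875, 0.625 and 0.375. Relative efficiency is 0.385/0.875 = 44%, then 60% and 76%.

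Both fall short of T1 adjustment. Which is worse depends on r.

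**Imbalance at T1.** Suppose the arms differ by Δ at T1. If the difference is chance, the expected carry-over to follow-up is rΔ, which the covariate removes and a follow-up-only comparison keeps. If it is a stable selection difference, all of Δ persists. Adjustment with slope r then removes only the fraction r (30%, 50%, 70%), while a change from T1 removes all of it.

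**The case against.** The strongest reply is that this is one condensed sentence in an article. It does not say that T1 is a response wave, nor that T1 is ruled out as a covariate, and such detail is often left to the analysis plan. That stands in part. A reader might infer that T1 is pooled into the group comparison as a no-effect wave, but the text does not say so. Dilution affects only the group main effect, and the wording about each follow-up points to per-visit comparisons. What remains is that the article commits to a method without conditioning on T1, and no reading of that method recovers the lost precision.

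A second reply is that the gain from 0.80 to 0.84, 0.90 or 0.98 is measured against follow-up-only analysis. That is correct. If the ANOVA is read as change from T1, the comparator is 0.66, 0.80 and 0.95, and at r = 0.7 the gain is small.

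A third reply is that recruitment after randomisation favours change-type contrasts. This also stands in part: T1 adjustment should not be presented as a cure for selection differences.

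**Conclusion.** The point holds as one of efficiency for secondary outcomes, worth correcting but not a validity error. For knowledge, practice/attitude and self-efficacy, conditioning on T1 is more precise than any of the three tests the stated ANOVA could support. At r = 0.5 both single-visit alternatives need a third more students than the covariate analysis.

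The size rests on the assumed r, on equal correlation between waves, and on a d taken from another outcome. The protocol makes no power claim for these scores. For practice items, T1 counts taken before anyone is taught the model may predict later counts poorly; with r near 0 there would be almost no gain over follow-up only.

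A reader might conclude that the primary analysis or the 368 is undermined. The documents do not support that: the sample size reproduces, it is built on the T4 referral count, and no T1 value is described for that count. Nor does this argument support any particular covariate list for the logistic or referral models.

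**What to change.** For objectives 2–4, replace the mixed ANOVA with a linear mixed model on T2–T5. Use the T1 score, group, visit and group-by-visit as fixed effects, and school and student as random effects. Report the adjusted group difference with its confidence interval at each visit. State explicitly that T1 is a covariate and not a response wave.

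Add a change-from-T1 sensitivity analysis, and say that T1 adjustment addresses chance imbalance but only partly removes differences from recruitment after randomisation.

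The cost is a rewritten sentence in Data analysis, best settled before outcome data are examined. The T1 scores are already collected and the linear mixed models procedure in SPSS can fit the model. The primary outcome and the sample size need no change on this account.

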Apart from resolving the myths in youngsters, a literature review revealed that brief interventions and referrals are important strategies to assist smokers to receive professional help to quit smoking successfully, as supported by the World Health Organization (WHO) and previous publications [10–12]. Particularly, the AWARD (Ask, Warn, Advise, Refer, Do-it-again) model emphasizes referrals and offers a brief and effective intervention for smoking cessation [11]. For instance, the Council on Smoking and Health and the Education Bureau in Hong Kong conducted the Smoke-free Elite Teens Program (formerly known as the Smoke-free Teens Program) [13, 14]. This program aims to nurture young people aged 14–18 years to promote a smoke-free culture in Hong Kong by firstly teaching participants the AWARD model and updated information on tobacco control, then requiring them to organize smoke-free programs in the community [13, 14]. The program has gained support from over 160 secondary schools, youth centers, and uniform groups. Nevertheless, the referrals rate was low with 1% of participants had referred smokers to smoking cessation services after the program [13]. One key possible reason is that the program did not provide hands-on experience to participants to proactively approach smokers and use the AWARD model. Some reported that they felt embarrassed and did not know how to effectively advise smokers to quit or refer smokers to professional services. Evidence also shows that hands-on experience is needed to effectively deliver learned skills [15].

In order to provide hands-on experience to youngsters, using service-learning model may be a suitable strategy [7, 16]. Service-learning models are used in some existing smoking cessation services such as Youth Quitline (YQL) [7]. YQL [7, 17] is a telephone hotline funded by the Department of Health in Hong Kong to train undergraduate nursing students to provides free peer smoking cessation counseling to young smokers aged 25 years or below. The quit rate in YQL is high [6], which represents a major success when compared with earlier results and other smoking cessation services in Hong Kong [6, 18]. YQL may be an appropriate venue for youngsters to gain hands-on experience of the AWARD model.

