### Aim and objectives

This study aims to promote smoking cessation by training young people as anti-smoke ambassadors (ASAs) with increased knowledge on smoking cessation and skills using the AWARD model to build community capacity in smoking cessation.

The objectives are to: 1) examine the effectiveness of our program in assisting secondary school students to refer smokers to YQL (primary objective), 2) increase ASAs’ knowledge about smoking cessation and skills using the AWARD model, 3) enhance their practice and attitudes toward smoking cessation and AWARD model, 4) increase their self-efficacy in using AWARD model skills, 5) provide hands-on experience in using the AWARD model through the service-learning model, 6) train ASAs to deliver brief interventions to young smokers using the AWARD model, and 7) identify facilitators and barriers in implementing in the real-world.

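### The primary outcome, referrals per student at T4, is assigned to two unranked analyses, and neither is the T4 comparison of mean counts, allowing for schools, on which the sample size rests

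*Protocol article*

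**What the plan says.** The Outcomes section fixes a count at one time point: "The primary outcome will be the number of smokers who referred by secondary school students to YQL at T4", the end of the 6-month competition. The Aim and objectives section makes this objective 1, to "examine the effectiveness of our program in assisting secondary school students to refer smokers to YQL (primary objective").

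The Data analysis section covers objectives 1 to 4 in one sentence. It names a mixed between-within ANOVA together with logistic regression (reported as odds ratios), and says that they "will be used to examine the differences in outcomes between the ASAs and the control group (objectives 1–4) at each follow-up". It does not divide the two methods among the objectives, rank them or single out T4. It also does not turn the referral count into a yes/no outcome.

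The Sample size calculation section uses a standardised difference of d = 0.35 in the number of smokers referred at 6 months. It then applies a design factor for schools (intracluster correlation 0.01, 28 students per school).

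The only referral rate in the document is in the Introduction, for an earlier programme that taught the AWARD model without hands-on practice: "the referrals rate was low with 1% of participants had referred smokers to smoking cessation services after the program". The control arm here also receives AWARD teaching without hands-on sessions.

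**The concern.** Three different quantities are attached to one primary objective. The sample size concerns a difference in mean counts at T4. The logistic regression concerns the odds of some event that is not defined, presumably any referral against none. The ANOVA yields a group effect and a group-by-time effect, and neither is identified as the primary contrast. These can disagree. An arm in which a few students refer many smokers may differ in mean count but hardly in the proportion who refer. With no ranking, the deciding test could be chosen after the data are seen.

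Logistic regression carries a further risk. If referral in the control arm is as rare as in the earlier programme, that arm may contain no referring student, and the ordinary odds ratio then has no finite estimate. The named method could fail to show an effect just when the contrast between arms is greatest.

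**Working it through.** **1. What the sample size tests.** Inputs from the Sample size calculation section: d = 0.35, 5% significance, 80% power, design factor 1.27, 10% attrition.

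- Two-sided two-sample t-test: 129.11, so 130 per arm and 260 in total. This reproduces the stated 260. A one-sided test would give 204, so two-sided is implied.
- Design factor: 1 + (28 - 1) × 0.01 = 1.27, and 260 × 1.27 = 330.2, so 331.
- Attrition: 331 / 0.9 = 367.8, so 368, or 184 per arm.

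The stated figures all reproduce. They rest on a two-group comparison of mean counts at one time point with an allowance for schools. That is neither a group-by-time test nor an odds ratio.

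**2. Chance that no control student refers anyone.** If a proportion p of controls refers at least one smoker and students are independent, the chance is (1 - p)^n. I take n = 184 (all randomised controls) and n = 165 (about 331 / 2, after 10% attrition). Only p = 1% comes from the document; the other rates are assumptions to show the range.

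| Control rate p | n = 184 | n = 165 |
|---|---|---|
| 0.5% | 0.995^184 = 39.8% | 0.995^165 = 43.7% |
| 1% | 0.99^184 = 15.7% | 0.99^165 = 19.0% |
| 2% | 0.98^184 = 2.4% | 0.98^165 = 3.6% |
| 3% | 0.97^184 = 0.4% | 0.97^165 = 0.7% |

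At 1% the expected number of referring controls is 184 × 0.01 = 1.8, or 165 × 0.01 = 1.7. Clustering raises the chance a little. With a beta-binomial model, intracluster correlation 0.01 and 7 schools, it is 19.3% for n = 184 and 22.3% for n = 166.

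**3. What logistic regression then reports.** Take 0 of 184 controls and 15 of 184 intervention students as referrers (the 15 is assumed). The maximum-likelihood fit does not converge: the log odds ratio drifts to about 18 with a standard error of about 2400, and the Wald p-value is 0.99. Fisher's exact test on the same table gives p = 0.00005.

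**4. The group-by-time test.** The visits are T1, then "at the end of training program (T2), and at 3 (T3), 6 (T4), and 12 months (T5) after the end of the training program". A group-by-time test over several visits asks whether the arm difference changes at all across them, not whether the arms differ at T4. I simulated it with no true effect, under these assumptions: negative-binomial counts with mean 0.1 and dispersion 0.2, 166 per arm, no clustering, zero at T1 and T2, cumulative counts at T3 and T4, and T5 equal to T4. The uncorrected test rejected in 11% of trials, the Greenhouse-Geisser corrected test in 5.2%, and a t-test at T4 alone in 5.3%.

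**The case against.** The strongest reply is that this is a condensed article. One sentence serves four objectives, the natural reading is ANOVA for scores and logistic regression for yes/no items, and a separate analysis plan may map methods to outcomes. That reading is fair, but it leaves objective 1 without a matching method, because a count is neither a score nor a yes/no item. Nor is the text merely silent: it names methods for objective 1, and they do not fit the stated outcome.

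It can also be said that comparing the arms at each follow-up includes a comparison of means at T4. That stands in part. Such a comparison would be close to the powered quantity, but the text does not name it as the deciding one and does not mention schools in the analysis.

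Four stronger readings are tempting and are not supported.

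- A reader might infer a five-visit ANOVA of referrals, diluted by visits before any referral is possible. The Measurements section gives T1-T5 only for knowledge, practice and attitudes, and self-efficacy; referrals are placed at T4 and T5. Even if such an ANOVA were run, averaging shrinks the standard deviation along with the difference. In simulations with assumed negative-binomial counts, power for the averaged group effect was within 0.7 percentage points of the T4 test.
- A reader might infer that two unranked tests nearly double the false-positive rate. Both use the same T4 counts and are strongly correlated. Simulated rejection by either test under no effect was 4.6% to 7.8%, for assumed mean counts of 0.05 and 0.2.
- A reader might infer that skewed counts invalidate any comparison of means. With equal arms of 166 and no clustering, the T4 comparison above kept its level, and the document does not say that an ANOVA would go uncorrected.
- A reader might infer that the logistic regression will fail. The 1% comes from a different programme, and at 3% or more an empty control arm is unlikely.

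**Conclusion.** The point holds as a mismatch between the primary outcome and its stated analysis. Two methods are named for objective 1 without a ranking or a dichotomy, and neither is the school-adjusted T4 difference in mean counts that was powered. This part rests on the text alone.

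The risk of an inestimable odds ratio is conditional. It is about 16-19% at the 1% rate and falls quickly above that rate. The figures assume independent students, 184 to 165 analysed controls, and a control rate for which the document gives only one indirect value. The sample size arithmetic is not in question.

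**What to change.** Name one primary analysis in the Data analysis section: the between-arm difference in YQL-confirmed referrals per student at T4, tested on the 14 school mean counts. Use a permutation test that respects the randomisation blocks, or an equivalent school-level analysis with small-sample inference. It stays valid with no control referrals, allows for schools, and keeps the quantity that was powered.

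Report two supportive analyses: a negative-binomial rate ratio with a school random intercept, and any referral against none by penalised logistic regression allowing for school. The negative-binomial model should not be primary. Its rate ratio also has no finite estimate when the control arm is empty, and it changes the effect measure behind the sample size. Keep repeated-measures models for the knowledge, attitude and self-efficacy scores.

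The cost is a change of wording, a little more analysis work, and fewer degrees of freedom: 14 - 2 = 12 for a school-level t-test. No added students, schools or visits are needed to state it.
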